### Intervention groups

Volunteers will participate in a multicomponent exercise program combining supervised and home-based exercise for 12 weeks, three times per week, 60 min per session. Participants will be divided into (1) supervised exercise (SUP), who will attend supervised group sessions at the training center; (2) home-based exercise (HB), who will participate in individual sessions at home; (3) supervised plus home-based exercise (SUP+HB), who will attend to one session per week at the training center and two sessions per week at home. Physical educators or physiotherapists will guide the supervised sessions at the training center.

The volunteers who will attend home sessions (HB and SUP+HB) will have an initial visit to their home to receive recommendations about how to perform the exercises safely. A guide with illustrations and instructions to reinforce proper exercise execution will be provided to each participant with space for recording the sessions performed and possible occurrences. On this occasion, they will receive ankle cuff weights (1, 2 and, 4 kg) to the strength training and a square stepping for walking exercises. To control program adherence, participants will record the days they complete the program, and they will also receive messages with incentives to perform the exercises at home.

The exercise program will consist of functional exercises of muscle strength, balance, flexibility, and gait, based on the recommendations of Singh et al. [16] and American College of Sports Medicine [17] (ACSM). Each session will be divided into 05 minutes of dynamic and articular warm-up, 10 minutes of dynamic and static balance exercises, 25 minutes of muscle-strengthening exercises, 10 minutes for gait exercises, and 10 minutes of flexibility exercises.

The exercise program will consist of four phases: phase 1 (1 to 3 weeks), phase 2 (4 to 6 weeks), phase 3 (7 to 9 weeks) and, phase 4 (10 to 12 weeks). Each phase will differ in the load and difficulty level of exercises, as shown in Table 1. The session intensity will be measured by the rate of perceived exertion (RPE) according to Borg Scale (6–20). In all groups analyzed, an explanation regarding the scale will be provided as well as a familiarization with the protocol before the start of interventions. Those measurements will be analyzed in different moments of the session, aiming to characterize the intensity perceived. In all training sessions, the volunteers will be encouraged to perform the exercises respecting the 1:3 ratio for strength exercises[18].

**Table 1 pone.0259827.t001:** Multicomponent exercise program planning.

Modality	Balance Training	Resistance Training	Gait Training	Flexibility Training
**Volume**	1–2 sets of 4–5 different exercises emphasizing static and dynamic postures for 30 seconds	**Phase 1:** 3 sets of 12 repetition, 1-min interval between sets **Phase 2**: 3 sets of 10 repetition, 30-s interval between sets **Phase 3:** 3 sets of 8 repetition, 1-min interval between sets **Phase 4**: 3 sets of 8 repetition, 30-s interval between sets.	1 set 5 repetition 6 gait exercises	Sustain stretching exercises for 20 sec to each major muscle groups
**Intensity**	Progressive difficulty with increases in complexity **Phase 1:** reduction of foot support base. **Phase 2**: unstable surface. **Phase 3:** reduction of visual information. **Phase 4:** objects manipulation.	**Phase 1:** 13–15 on the Borg Scale. **Phase 2 to 4**: 15–17 on the Borg Scale.	**Phase 1 to 4:** 12–13 on the Borg Scale (40–60% of heart rate reserve)	**Phase 1 to 4:** Progressive neuromuscular facilitation technique, which involves stretching as far as possible, then relaxing the involved muscles, then attempting to stretch further, and finally holding the maximal stretch position for at least 20 seconds.
**Exercises**				
	Static exercises: single-leg, semi-tandem, and tandem position, single-leg stand with knee elevation. Dynamic exercises: perform forward, backward, and lateral walking in plantarflexion, dorsiflexion, and tandem position. Transfers of chairs, move over objects, and step-ups.	**Phase 1 and 2:** Sit-to-stand a chair; Standing knee; Pelvic lift; Wall sitting isometric; Sitting ankle plantar flexion; Standing ankle plantar flexion; Barbell curl; Bend-over dumbbell row; Halter front raise; Lying hip extension; Lying hip flexion; Sit-up; Walking lunges; Standing knee flexion; Standing hip extension; Hip adductor Exercise; Hip abductor Exercises **Phase 3 and 4:** Wall sitting isometric; Barbell curl; Bend-over dumbbell row; Sit-up; Walking lunges; Standing knee flexion; Squat; Seated Knee Extension; Pelvic lift; Standing hip flexion; Standing calf raise; Bent over row; Dumbbell curls; Dumbbell Side Lateral Raise; Hip extension; Stiff legged deadlift; Step-Ups; Abductor Exercises; Adductor Exercise.	Walk at the usual and maximum speed, and exercises involving square stepping. The square-stepping Exercise was based on the study conducted by Shigematsu colleagues (2008).	Exercises involving major muscle groups, including hip and knee flexion and extension, and abduction and adduction. Besides the addition of upper limb stretching movements.

The training protocol will be modified if the participant undergoes severe pain or discomfort when carrying out the training program. Besides, the protocol will be interrupted if the participant is committed to any illness that may prevent exercise execution.

Aiming to enhance the validity of the presented data, several methods will be used to assess exercise protocol adherence, including engagement in the supervised exercise sessions, filling a calendar in the home sessions, and weekly calls to remember the importance of performing the exercise.

### Measurements

The evaluation sessions will be conducted in the biomechanics laboratory in CECOM at UFPR, where trained evaluators will administer the tests. The evaluators responsible for applying the exercise program will not participate in evaluating the sample, aiming to guarantee a simple blind study. The steps and timeline of the assessments can be observed in Fig 2.

**Fig 2 pone.0259827.g002:**
[figure not shown]
Representation of the timeline and assessments of the study.

All participants visited the laboratory on two nonconsecutive days with a minimum of 48 hours of resting to perform baseline evaluations. In the first visit, participants will be requested to answer a clinical anamnesis, followed by an anthropometric assessment. All protocols applied for primary and second outcomes will be described below.

### Primary outcomes

#### Muscle isokinetic strength

The evaluation of muscle isokinetic strength will be performed using the Biodex Multi-joint System dynamometer (Biodex Medical Systems. Inc. Shirley. NY. USA). The protocol includes two sets of three repetitions of the knee, hip, dorsiflexion, and plantarflexion concentric flexion/extension movements at 60°/s and 180°/s of dominant limb, with a two-minute interval between sets [19]. Participants will be positioned following the Biodex factory specifications, which are described by Symons et al. [20].

Each test will be performed twice at the same evaluation session, with different verbal commands of the evaluator: in the first test, a submaximal set will be used for familiarization, followed by a second test, which will be held with maximum strength for the record. Data will be acquired at 1000 Hz, and all muscle strength tests will be analyzed using the Biodex System 3 Advantage software, version 3.2. The variables analyzed will be peak torque/body weight, total work, and average power.

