**Methods:**

This protocol is a randomized controlled clinical trial with a sample of 66 older adults divided into three groups: supervised exercise (SUP = 22), home-based exercise (HB = 22), and supervised plus home-based exercise (SUP+HB = 22). The multicomponent exercise program will last 12 weeks, three times per week, for 60 min per session and include warm-up, balance, muscle-strengthening, gait, and flexibility exercises. The study’s primary outcomes will be neuromuscular function, composed of the assessment of muscle isokinetic strength, muscle architecture, and neuromuscular electrical activation. The secondary outcome will be physical function, usual and maximum gait speed with and without dual-task, and quality of life. All outcomes will be assessed at baseline and post-intervention (week 12).

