The first stimulation will be delivered during an MVIC, which will be nominated as the superimposed twitch. Followed the first stimulation, a second stimulus will be given 3 s after the MVIC, being nominated as the potentiated twitch. Both the STw and the PTw amplitudes allowed the VAL quantification, as proposed by Merton (1954). The variables analyzed will be the peak torque, contraction time, torque development rate analyzed through the formula (RTD = PT/CT), half-relaxation time, and VAL.

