#### Muscle architecture

The muscle architecture (fascicle length, pennation angle, and muscle thickness) of MG muscle of dominant limb will be assessed using an ultrasound (Konica Minolta Medical Imaging Inc [name], Wayne, NJ, USA) in B mode with linear arrangement transducer (4 cm height x 2 cm length, 10 MHz), with the depth adjusted to 4 cm for the MG.

The image of MG will be performed with the participant resting in the prone position, with the feet hanging from the edge, and an ankle joint angle at 15° dorsiflexion will be fixed. The ultrasound transducer will be positioned at 30% of the portion between the fibula’s lateral malleolus and the lateral condyle of the tibia [25]. The transducer will be oriented in the axial plane, aligned perpendicularly to the muscle, and moved from the center to the lateral position along with templates demarcated on the skin.

It is important to highlight that the gastrocnemius muscle is essential to maintain independence, gait speed and reduce falls risk. However, the aging process causes a muscle architecture alteration, reducing the cross-sectional area, pennation angle, and fascicle length. These age-related alterations resulting in a reduction of strength and muscle power, gait speed and functionality [26].

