### Statistical methods

For data analysis, the results will be reported using descriptive statistics and mean and standard deviation. All data will be analyzed by intention-to-treat, with baseline scores substituted for missing follow-up data. The Shapiro-Wilk test will be applied to verify the normality of the data and the Levene test for the sample’s homogeneity. For parametric data, a comparison between groups and periods (pre and post-training) will be analyzed by an ANOVA of mixed-models with Bonferroni’s post-hoc test. When differences between groups were observed at the baseline, a covariance analysis (ANCOVA) will be applied. In addition, a Pearson’s correlation coefficient (r) was calculated to verify the magnitude of the possible observed effects, considering r = .10 as a small effect, r = .30 as a medium effect, and r = .50 as a large effect [34]. P-values less than 0.05 will be considered statistically significant. The tests will be performed using the IBM SPSS Statistics software version 25.

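### Every strength, twitch and architecture variable is primary and each is tested at 0.05, so the stated type I error does not hold for a claim about neuromuscular function

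*Protocol article*

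**What the plan says.** The Abstract (Methods) states that the "primary outcomes will be neuromuscular function, composed of the assessment of muscle isokinetic strength, muscle architecture, and neuromuscular electrical activation". The Primary outcomes section then has one subsection per domain.

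- **Muscle isokinetic strength.** The test protocol is "two sets of three repetitions of the knee, hip, dorsiflexion, and plantarflexion concentric flexion/extension movements at 60°/s and 180°/s of dominant limb". For these, "The variables analyzed will be peak torque/body weight, total work, and average power".
- **Neuromuscular function.** "The variables analyzed will be the peak torque, contraction time, torque development rate analyzed through the formula (RTD = PT/CT), half-relaxation time, and VAL". That makes five.
- **Muscle architecture.** The measures are "muscle architecture (fascicle length, pennation angle, and muscle thickness) of MG muscle of dominant limb".

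No variable is singled out as the lead, and there is no composite score, hierarchy or rule for combining results.

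Statistical methods plans a mixed-model ANOVA over groups and periods with a Bonferroni post-hoc test, and says "P-values less than 0.05 will be considered statistically significant". Sample size uses one effect size of 0.25 and a type I error of 0.05, and names no outcome to which they apply.

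**The concern.** The type I error of 0.05 used to size the trial is the error rate of one test. The article attaches primary status to a long list of variables and gives each the same threshold. A Bonferroni post-hoc test inside an ANOVA adjusts the comparisons between groups and periods for that one variable. On the usual reading it does nothing about the number of variables analysed.

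The Introduction and Discussion hypothesise that SUP+HB will do better than HB and similarly to SUP on neuromuscular function as a whole. With no deciding variable, a positive statement about that construct could rest on whichever variable falls below 0.05. A reader would then take as a confirmed primary result something whose real error rate is well above 0.05.

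**Working it through.** **Step 1. The plan's own figure.** Inputs from Sample size: effect size 0.25 (read as Cohen's f), alpha 0.05, 0.95 (printed as type II error, read as power), 3 groups, 3 measurements, correlation 0.5 (read as the correlation among repeated measures), loss 20%. For the group-by-time interaction, λ = N·m·f²/(1−ρ), df1 = (g−1)(m−1), df2 = (N−g)(m−1). At N=54 and m=3, λ = 54×3×0.0625/0.5 = 20.25 with df 4 and 102, and power is 0.958. Then 54×1.2 = 64.8, which is 66 in equal groups. So 66 is reproduced as the size for **one** three-group interaction test at 0.05. (The article plans two assessments, not three. That is a separate matter; power below is computed for two.)

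**Step 2. How many primary variables.**
- Printed variable types: 3 isokinetic + 5 twitch + 3 architecture = 11.
- With each movement and speed separate, the count depends on how "knee, hip, dorsiflexion, and plantarflexion concentric flexion/extension movements at 60°/s and 180°/s of dominant limb" is read:
  - Knee flexion and extension, hip flexion and extension, dorsiflexion, plantarflexion: 6×2×3 = 36; 36+5+3 = **44**. This is the most natural reading.
  - Four movements only: 4×2×3 = 24; 24+8 = **32**.
  - Four items, each in two directions: 8×2×3 = 48; 48+8 = **56**.

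Only the 11 types are printed. The larger counts are derived.

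**Step 3. Chance of at least one false positive.** If the tests are independent and nothing truly differs, it is 1 − 0.95^k:
- k=11: 0.431
- k=32: 0.806
- k=44: 0.895
- k=56: 0.943

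These variables will be positively correlated, so the independent figures are upper values. Simulation of one-way F tests on change scores (22 per arm, no true effect, common correlation assumed) gives:

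| Common correlation | 11 variables | 44 variables |
|---|---|---|
| 0 (exact) | 0.43 | 0.90 |
| 0.3 | 0.38 | 0.77 |
| 0.5 | 0.32 | 0.62 |
| 0.7 | 0.23 | 0.40 |
| 0.9 | 0.14 | 0.20 |

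Repeat runs differ by about 0.02. With 44 variables in blocks, correlations of 0.7 within and 0.3 between blocks give 0.67, and 0.8 within and 0.5 between give 0.53. The expected number of false positives does not depend on correlation: 0.05×11 = 0.55, or 0.05×44 = 2.2.

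**Step 4. What adjustment does to power.** Two measurements, f=0.25, correlation 0.5, N=66: λ = 66×2×0.0625/0.5 = 16.5, df 2 and 63.

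| Level | Power, N=66 | Power, N=54 |
|---|---|---|
| 0.05 (one lead variable) | 0.953 | 0.902 |
| 0.05/3 = 0.0167 (strictest Holm step, three lead variables) | 0.889 | 0.796 |
| 0.05/44 = 0.00114 (all 44 kept primary) | 0.617 | 0.458 |

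N=54 stands in for the sample left after roughly 20% loss (66×0.8 = 52.8).

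**The case against.** Several parts of the opposing case stand and limit the point.

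- **The count.** A reader might infer that the plan commits to 44 primary tests. It does not say so. It prints 11 variable types and never states that each movement-by-speed cell is tested separately. The count has to be given as a range.
- **Likelihood.** A reader might also infer that a false positive is more likely than not. That fails at high correlation: for 44 variables the figure is 0.40 at 0.7 and 0.20 at 0.9, and for 11 variables it never reaches one half. High correlation is plausible for parts of the set. The rate of torque development is computed from two other listed variables, and peak torque, work and power come from the same repetitions.
- **Success rule.** The familywise rate applies only if one significant variable is enough. The article states no such rule. If every domain had to agree, the calculation would not apply.
- **Source of the effect size.** The 0.25 is taken from a cited study. The article ties it to no variable, but whether that study does cannot be checked here.

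One part does not stand: that the gap may be left to a full protocol or analysis plan. The article does not stay silent. It labels all these variables primary and fixes one threshold for every test. Naming a lead variable later would change the stated primary outcome, not add detail to it.

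**Conclusion.** The point holds in this form: followed as written, with any significant primary variable able to support the claim, the plan does not keep the 0.05 error rate used in its sample-size calculation. The chance of at least one false-positive primary result is about 0.14 to 0.43 for the 11 printed variable types and 0.20 to 0.90 for 44 variables. The lowest of these is nearly three times 0.05 (0.14/0.05 = 2.8). The size of the excess is uncertain because both the correlations and the exact count are assumptions; its direction is not. One test per variable is also a minimum, since a mixed ANOVA yields group, time and interaction tests and the article does not say which one decides.

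**What to change.** Before data are seen, name one lead primary variable, or one per domain with Holm adjustment across the three. Which variable leads is for the investigators to choose.

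Test it with the three-group group-by-time effect, the test that reproduces 66. Follow it with the planned Bonferroni pairwise contrasts, including SUP+HB vs HB and SUP+HB vs SUP, so that both parts of the hypothesis are addressed. Making SUP+HB vs HB the sole primary contrast would drop the similarity hypothesis and would no longer match the test behind the sample size.

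State that the 0.05 level and the effect size of 0.25 refer to the lead variable, and justify 0.25 for it. Report the remaining strength, twitch and architecture variables as secondary or mechanistic, with confidence intervals and no confirmatory claim.

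The cost is wording in the protocol and the registry, for which Trial design already gives a route (report to the ethics committee and update the registry). No measurement is lost, but the other variables lose confirmatory status. One lead variable costs no power. With three under Holm, power at the strictest step falls from 0.95 to 0.89 at N=66 (f=0.25, correlation 0.5, two measurements).

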#### Neuromuscular function

The neuromuscular function will be evaluated using an isokinetic dynamometer Biodex along with surface electromyography (EMGs). Aiming to determine the voluntary activation level (VAL), the twitch interpolation technique will be used [21]. The present study protocol will stimulate the posterior tibial nerve, activating the sural triceps muscles (soleus and gastrocnemius) [22].

For the acquisition of EMG signals, an electromyograph (Trigno Wireless, Delsys, USA) will be used, with an electric stimulator (Neuro IOM-Neurosoft®) with bipolar surface electrodes AMBU Neuroline 715. The muscle analyzed will be the lateral gastrocnemius (LG) and medial gastrocnemius (MG) of the dominant limb, and the electrode placement process will follow the Surface EMG for the Non-Invasive Assessment of Muscles (SENIAM) recommendations [23,24]. Electrodes will be placed on the LG, MG, and tibialis anterior [23].

The reference electrode will be placed in a central position at the same leg of the stimulation, and an electrode for electrical stimulation will be placed over the patellar tendon. For the stimulation of the posterior tibial nerve, the cathode will be placed in the popliteal fossa.

After the electrodes are placed, the participant will be positioned on the isokinetic dynamometer to evaluate the ankle, as described by Symons et al. (2004). Data collection will be carried out during maximum voluntary isometric contraction (MVIC), which will consist of three maximal contractions of five seconds each.

The VAL will be analyzed through two supramaximal doublets (two electrical stimulation with 200 μs pulse width, 10 ms interstimulus interval, and 1000 mA maximum output) applied percutaneously femoral nerve during the MVIC. The optimal stimulation intensity will be determined from the M wave and strength measurements before each test session. The stimulation intensity will increase by five mA until there is no further increase in the peak force contraction. Therefore, an addition of 30% of the highest value will be added to assure a supramaximal stimulation.

The first stimulation will be delivered during an MVIC, which will be nominated as the superimposed twitch. Followed the first stimulation, a second stimulus will be given 3 s after the MVIC, being nominated as the potentiated twitch. Both the STw and the PTw amplitudes allowed the VAL quantification, as proposed by Merton (1954). The variables analyzed will be the peak torque, contraction time, torque development rate analyzed through the formula (RTD = PT/CT), half-relaxation time, and VAL.

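### The protocol contradicts itself on which nerve is stimulated for voluntary activation of the calf, and the only ultrasound plane it states cannot show fascicle length or pennation angle

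*Protocol article*

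**What the plan says.** The abstract of the Protocol article makes neuromuscular function the primary outcome, made up of isokinetic strength, muscle architecture and neuromuscular electrical activation. The two instructions at issue stand under Primary outcomes.

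**Nerve stimulated (Neuromuscular function).**
- The section opens the method with "The present study protocol will stimulate the posterior tibial nerve, activating the sural triceps muscles (soleus and gastrocnemius").
- It repeats the nerve when it places the electrodes: "For the stimulation of the posterior tibial nerve, the cathode will be placed in the popliteal fossa".
- The recording sites match: "The muscle analyzed will be the lateral gastrocnemius (LG) and medial gastrocnemius (MG) of the dominant limb".
- So does the joint: "the participant will be positioned on the isokinetic dynamometer to evaluate the ankle".
- The sentence that fixes the VAL stimulus (two supramaximal doublets, with pulse width, interval and maximum output) then says they are "applied percutaneously femoral nerve during the MVIC".
- VAL is computed from the superimposed twitch (STw) and the potentiated twitch (PTw): "Both the STw and the PTw amplitudes allowed the VAL quantification".

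**Scan plane (Muscle architecture).**
- The variables are "The muscle architecture (fascicle length, pennation angle, and muscle thickness) of MG muscle".
- The acquisition is "The transducer will be oriented in the axial plane, aligned perpendicularly to the muscle, and moved from the center to the lateral position". The section describes no other orientation of the probe.

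**The concern.** In both places the written instruction does not lead to the variable it is meant to give.

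Twitch interpolation works only if the stimulus reaches the muscle whose torque is recorded. A doublet to the femoral nerve, recorded as ankle torque with gastrocnemius EMG, says nothing about activation of the calf. For the ultrasound, fascicle length and pennation angle are properties of the fascicles seen along their length, and a slice across the muscle does not show them.

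These are primary outcomes, and the trial's stated novelty is the neuromuscular mechanism behind strength gains. Later analysis cannot repair the loss: a calf twitch or a longitudinal image that was not obtained at baseline cannot be recovered after 12 weeks of training.

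**Working it through.** The point contains no sample size, power or error rate, so there is no figure to reproduce. The check sets each instruction beside the variable it serves. It uses only two outside facts, both general anatomy and geometry: the femoral nerve supplies the knee extensors and not the calf, and a cross-section does not display structures that run along the muscle.

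**1. Nerve.**

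| Element in Neuromuscular function | Stated | Points to |
|---|---|---|
| Nerve, opening statement | posterior tibial | calf |
| Target muscles | soleus and gastrocnemius | calf |
| Cathode | popliteal fossa | calf |
| EMG recording | lateral and medial gastrocnemius, tibialis anterior | lower leg |
| Dynamometer | ankle | calf |
| Site of the VAL doublets | femoral nerve | thigh |

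Five elements agree and one does not. The one that disagrees is the sentence that specifies the VAL stimulus and where it is applied. No stimulating electrode at a femoral site is described, so the section cannot be carried out consistently as it stands.

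If the femoral sentence were followed, the chain would be: no stimulus to the calf, hence no evoked plantarflexor twitch, hence neither the superimposed nor the potentiated amplitude that VAL requires. The section lists five variables: peak torque, contraction time, rate of torque development, half-relaxation time and VAL. Rate of torque development is defined as peak torque over contraction time, so it inherits any fault in those two. The count of five assumes that peak torque here means twitch torque, which its place in the list suggests but the text does not say. If it means the torque of the voluntary contraction, that one variable does not depend on the nerve.

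**2. Scan plane.**

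| Variable of the medial gastrocnemius | Plane needed | Plane stated | Readable? |
|---|---|---|---|
| Fascicle length | along the fascicles | axial | no |
| Pennation angle | along the fascicles | axial | no |
| Muscle thickness | axial is sufficient | axial | yes |

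Taken alone, the word perpendicular might refer to the angle between probe and skin. Together with the axial plane and a sweep from centre to lateral, it describes a cross-section. Such a sweep suits cross-sectional area, which the section mentions only as background on ageing and does not list as an outcome. So 2 of 3 architecture variables have no stated acquisition that could yield them.

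**3. What is not touched.** EMG recorded during the voluntary contraction does not depend on the nerve stimulated. Isokinetic strength and muscle thickness are measured without either faulty instruction. The sample size calculation uses neither.

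**The case against.** The strongest reply on the nerve is that one phrase is out of line with an otherwise consistent calf set-up, and that a competent evaluator would see this. The stimulus intensity is also set from the M wave and force before each test session, so a stimulus that missed the calf should show itself at that step. This stands as far as it goes. It makes a drafting slip the likely explanation, and it means a reader should not infer that the trial will test the calf by femoral stimulation or that its VAL data will be invalid. The documents support a contradiction, not that outcome. It does not remove the need to correct the operative sentence for a primary outcome.

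On the ultrasound, no sentence contradicts another, the article condenses a fuller protocol, and a longitudinal capture may be described there or in the source cited for the scan site. That possibility remains open. But the article does not merely leave the plane out: it states one, for all three variables, and that plane is wrong for two of them. The Measurements section also says that the methods for primary and secondary outcomes are described in what follows. A stated rule that does not fit its variable is a fair finding.

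Two stronger inferences are tempting and do not hold. The first is that pre-post change will be confounded with technique. Nothing in the article suggests that evaluators or visits would resolve the text differently, and a change of technique common to all three randomised arms would not by itself favour any arm. The second is that every primary domain other than isokinetic strength is lost in all 66 participants. Muscle thickness and voluntary EMG survive, and the 66 already includes an allowance for 20% loss.

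**Conclusion.** The point holds as two separate defects of unequal kind.

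- **Nerve:** an internal contradiction within one section, probably a slip, in the sentence that defines the VAL stimulus. It bears on VAL and on up to four further variables from the same test.
- **Scan plane:** a stated acquisition that cannot give two of the three architecture variables. It rests on scan geometry and on reading the described scan as the only one. A longitudinal scan documented elsewhere would reduce it to a wrong statement in the article.

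The stakes are the validity of primary-outcome measurement. No power, error rate or planned analysis changes. Because both instructions govern data that cannot be collected again after the intervention, they should be settled before the first baseline assessment. If assessments have begun, the technique actually used should be stated.

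**What to change.** 1. In Neuromuscular function, reconcile the text to one nerve throughout, consistent with the muscle studied, the electrode sites and the joint on the dynamometer.
2. In Muscle architecture, specify a longitudinal image in the plane of the fascicles, at the same site and joint angle, for fascicle length and pennation angle. Keep the axial sweep only for a variable that a cross-section can give.
3. State that the same instructions apply at baseline and at week 12, and carry both corrections into any testing manual.

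The cost is the correction of two method paragraphs and any manual based on them. The probe is rotated within the same scan, so no extra visit, staff or device is needed. The Trial design section already commits the investigators to report any protocol change to the ethics committee and to update the registry entry.
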